### Description of the Study

The phases of the study are:

* **PHASE 1. Recruitment of primary care nurses (PCN)**: the project was presented to all the PCN within the study setting to recruit midwives interested in participating. Those who were interested in collaborating signed a document of commitment to participate in the study.

* **PHASE 2. Creation of the study groups (intervention-IG and non intervention-NIG) and midwife training programme**:

- The randomisation unit was the PCN. Using simple randomisation the centres distributed the IG and NIG at a proportion of 1:1.

- The formation of the participating midwives was carried out on 3 centralised work days during which the develpment of the study was explained in depth and they were given instructions on correct completion of the questionnaire on hygienic-dietetic habits in both a paper and electronic format. Each professional was assigned a support investigator to clarify any doubts which may arise during the study period. The objective of session was for the midwives to obtain sufficient training to avoid possible variability in the development of the study and in the collection and registration of data.

* **PHASE 3. Pilot study**: this was carried out in three randomly selected PCN with 30 pregnant women who were not included in the study in order not to affect the final results. This pilot study evaluated the study inclusion process of the pregnant women, data collection by paper and electronic questionnaire as well as the appointment circuit, referral and presentation of ioduria results.

* **PHASE 4. Recruitment of the pregnant women, initial evaluation and request for first ioduria (in IG and NIG)**:

- Recruitment of the pregnant women: the pregnant women will be consecutively recruited from the women attending consultation to the midwife until the number of 25 women required by each PCN has been reached. Each midwife will know the number of women that they must recruit for the study. If a pregnant woman fulfils the inclusion criteria the midwife will explain the study to her and will ask for her participation. If the woman accepts she will be given the study information sheet in which the objectives and the characteristics are described and she will be asked to sign the informed consent form to thereby be included in the study. If the woman refuses to participate the reasons for this will be noted, as will the administrative, sociodemographic and obstetric variables with the aim of determining the profile of this type of pregnant woman.

- Initial evaluation of the pregnant women: on the first contact with the women and through an individualised interview the midwife will collect the following variables: administrative, sociodemographic, obstetric, those related to smoking, consumption of foods rich in iodine, iodised salt and iodised multiple vitamins. All the data will be reported in an electronic data collection file (EDCF) which will include the rule of internal coherence to guarantee the quality control of the data. Following the interview the midwife will make an educational intervention on the importance of good alimentation during pregnancy and the repercussions this has on maternal and foetal health, with special emphasis on the importance of the consumption of foods rich in iodine and iodised supplements. An informative sheet will also be provided on the importance of iodine during gestation.

- Request for ioduria during the first trimester: the midwife will request an ioduria test and will explain the woman how to correctly collect the urine and will program the appointment for the second trimester visit of the pregnancy. On receipt of the ioduria results the midwife will note these in the EDCF. In cases in which iodine deficiency is detected the midwife will duly intervene, thus the reason for including the telephone number of the pregnant woman in the questionnaire. If iodine supplementation is indicated the administration will begin on collection of the first urine sample to avoid underestimation of the prevalence of iodine deficiency in the first trimester. Ioduria will be analysed using the Benotti&Benotti method performed in the laboratory of the Hospital Clinic of Barcelona.

* **PHASE 5. Group Education Intervention (only in IG)**: the coordinating midwives in each zone will be responsible for performing the educational workshops on hygienic-dietetic habits in the pregnant women in the intervention group. This workshop will be held in the first trimester since this is when organogenesis is produced and is therefore the time of greatest risk for the appearance of alterations in the development of the foetal central nervous system in cases of maternal iodine deficiency. The content of the educational workshop will be the same to avoid a variation in information and transmission of knowledge to the pregnant women, that is, to ensure receipt of homogeneous information by the pregnant women.

* **PHASE 6. Follow up (in IG and NIG)**: if a pregnant woman does not attend the appointment she will be called by telephone and if she cannot be contacted after 10 attempts she will be withdrawn from the study. The interview on hygienic-dietetic habits will be given in the second and third trimester appointments and determination fo ioduria will be requested. The reasons for participant withdrawal will be reported and a flow chart of the patients will be created throughout the study.

* **PHASE 7. Validation of the questionnaire on the iodine nutritional status in pregnant women**: the questionnaire has been elaborated by the investigator team after extensive review of the literature and finally based on the alimentary table according to iodine content (mcg/100 g) included in the monography on "Los alimentos y la salud" (Food and Health) (Egura R. Webb S. Tovar JL. Y Gausí C. Los minerales y la salud. Barcelona: Nuevas Ediciones de Bolsillo, S.L.; 2000. p 161-97). The questionnaire describes the foods with the greatest iodine content and the quantities consumed, the use of iodised salt and multiple vitamins containing iodine and smoking since the latter is a goitrogenic substance. Neither the origin of the foods nor the place in which the food is prepared is taken into account because of the impossibility to evaluate and confirm these aspects, despite the influence in the quantity of iodine consumed. Validation will be undertaken by an expert in psychometry from the Autonomous University of Barcelona (UAB) taking into account ioduria values.

* **PHASE 8. Completion of data collection**: after performing the third trimester appointment data collection will be concluded. The periodic controls of the data reported in the EDCF will have localised and corrected any incoherences that may have arisen.

* **PHASE 9. Data analysis and diffusion of the results**: the data obtained will be analysed and a final report will be elaborated with diffusion of the results in different scientific scenarios.

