## Methods/Design

### Design

Cluster randomised, controlled, multicentre trial. Randomisation unit: primary care team (PCT).

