### Setting

46 PCTs from the province of Barcelona that provide health coverage to urban, semirural and rural populations.

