### Sample size calculation

The sample size has been calcuated by multipying the size of a randomized simple design by the design effect. For the simple randomized design an alpha error of 0.05 and a beta error of 0.20 in a bilateral contrast are considered, requiring 204 pregnant women in the intervention group and 204 in the non intervention group to detect a difference greater than or equal to 15% in the prevalence of iodine deficiency between the two. After extensive review of the literature on group educational interventions in a pregnant population, the investigative team [37-40] considered that the intervention to be undertaken in the intervention group will achieve an improvement of at least 15% in hygienic-dietetic habits and thus in the levels of ioduria. A proportion of iodine deficiency of 44% in the non intervention group is assumed as indicated by studies performed in populations in the Pyrenees and the coast of the Maresme, areas near the study setting [18]. A loss to follow up of 15% has been estimated. Using an intracluster correlation coefficient of 0.05 [41-43], and based on an average of 25 pregnant women per PCT, the design effect is 2.2. Therefore, 898 pregnant women and 36 PCT are needed.

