## Discussion

One of the strengths of the present study is its design which is pragmatically oriented with respect to the needs of time and material resources.

Another strength of the study is the large number of midwives and patients involved, reinforcing the external validity of the data.

Since no register of women in the first trimester of pregnancy is available, selection of the study population can not be approached with a simple randomised sample but will rather be performed by consecutive sampling which could lead to a selection bias, the self-selection of the volunteer. To determine the possible presence of such a bias the administrative, sociodemographic and obstetric variables of the women who refuse to participate in the study will be analysed.

To increase the validity and reliability of the data collection of the hygienic-dietetic habits by individualised interview, the midwives have been especially trained in this task following a training session prior to initiation of the pilot study and a support investigator will be available to solve any doubts which may arise.

The difficulty in determining iodine intake through diet will be compensated by the determination of iodine levels in urine which is considered a good marker of iodine ingestion according to the WHO, UNICEF and ICCIDD [4,45].

To avoid the phenomenon of contamination which may appear when the intervention influences the subjects in the control group (frequent when the same work centre of the professionals belongs to different study groups), randomisation of the intervention will be performed by the PCN and not by study subjects. Although the unit of randomisation is the primary care unit, the intervention is given at the individual level and the outcomes are also measured at this level. The estimation of the design effect will be taken into account in all the main analyses.

Since participant losses and withdrawals randomly occur, any subject exclusion from the analysis may later affect group comparability. To preserve this all the patients included in the study will be evaluated according to the intention to treat principle and thus, all the patients will be analysed as pertaining to the group to which they were initially assigned independently of the treatment they have actually received.

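### The randomised unit and the quota of 25 women are given per primary care team in some sections and per primary care nurse in others; the design effect of 2.2 fits only if 25 is the number of women per randomised cluster

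*Protocol article*

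**What the plan says.** Team as the unit:
- The Design section reads "Randomisation unit: primary care team (PCT"), and the Abstract agrees.
- The Sample size calculation works per team: "based on an average of 25 pregnant women per PCT, the design effect is 2.2". It concludes: "Therefore, 898 pregnant women and 36 PCT are needed".

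PCN as the unit:
- Description of the Study, Phase 2: "The randomisation unit was the PCN".
- Phase 4, on recruitment: "until the number of 25 women required by each PCN has been reached".
- Discussion, on contamination: "randomisation of the intervention will be performed by the PCN and not by study subjects".

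The Phase 1 heading and the Abbreviations list both expand PCN as primary care nurses, and the Abbreviations list gives PCT its own entry. As defined, these are two different units. Data Collection records the midwife and the PCT as separate items and lists the number of midwives as a characteristic of the PCT, so a team may have more than one. No figure for midwives or nurses per team is given.

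**The concern.** Three things in a cluster trial depend on the unit: who is allocated together, when recruitment in a cluster stops, and how many women share a cluster when the sample is inflated. Here the label changes between the sizing section and the operational sections, and the figure of 25 moves with it.

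Read literally, the text allows two departures from what was sized:
- **Teams randomised, each nurse recruits 25.** A team with more than one recruiter is then a cluster larger than 25, and 2.2 understates the inflation needed.
- **Nurses randomised.** Colleagues in one team can be allocated to opposite arms. The Discussion names that situation as a source of contamination and presents the choice of unit as the remedy.

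The level at which the multilevel model has to account for clustering depends on the same answer.

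**Working it through.** **Inputs (Sample size calculation).** "an alpha error of 0.05 and a beta error of 0.20 in a bilateral contrast are considered"; 44% deficiency in the control group and a 15-point difference, so 29% in the intervention group; 204 women per group before clustering; 15% loss; intracluster correlation (ICC) 0.05; 25 women per PCT.

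**1. The plan's own figures reproduce.**
- Base size: 44% vs 29%, two-sided 0.05, power 0.80, with continuity correction, gives 174 per group. 174/(1 - 0.15) = 204.7, or 205, against the stated 204. The 15% loss is therefore already in the 204.
- Design effect: 1 + (25 - 1) × 0.05 = 2.2.
- Total: 204 × 2.2 = 448.8, rounded up to 449 per group; 2 × 449 = 898.
- Clusters: 897.6/25 = 35.9, so 36.

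**2. Teams randomised, 25 women per nurse.** The number of recruiting nurses per team (k) is an assumption. The ICC of 0.05 is kept at team level. Cluster size m = 25k; design effect = 1 + (m - 1) × 0.05; required N = 408 × design effect.

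| k (assumed) | m | Design effect | Required N | Teams at that N |
|---|---|---|---|---|
| 1 | 25 | 2.20 | 898 | 36 |
| 2 | 50 | 3.45 | 1,408 | 29 |
| 3 | 75 | 4.70 | 1,918 | 26 |

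**3. Power for k = 2 if the total is held at 898.**
- Teams: 898/50 = 18.
- Women after 15% loss: 898 × 0.85 = 763, or 382 per arm.
- Design effect: 3.45 at m = 50, or 1 + (42.5 - 1) × 0.05 = 3.075 if loss also shrinks the cluster to 42.5.
- Effective size per arm: 382/3.45 = 111, or 382/3.075 = 124.
- Power at 44% vs 29%: about 59% (111 per arm, with continuity correction) to 69% (124 per arm, without). On the same two conventions the plan as sized, 36 teams of 25, has about 80% to 86%.

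**4. Power for k = 2 if 36 teams are kept.**
- Women: 36 × 50 = 1,800; after loss 1,530, or 765 per arm.
- Effective size per arm: 765/3.45 = 222, or 765/3.075 = 249.
- Power: about 89% to 94%.

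The loss in step 3 therefore comes from having half as many teams. The larger quota alone does not cause it.

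**5. Nurses randomised.** With 25 women per nurse, the formula again gives 2.2 if 0.05 is the correlation within a nurse. The 36 would then count nurses, not teams, and any correlation between nurses of one team is not covered. Contamination in mixed-arm teams would dilute the effect; the document gives no figure from which to size that.

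**The case against.** The best reply is that PCN is a slip for the team or centre, and the context supports it:
- The sentence after the Phase 2 statement says that centres were distributed to the two groups.
- The pilot in Phase 3 was run in three PCN with 30 women, which reads as sites.
- Phase 4 adds that each midwife will know how many women she has to recruit, which fits a site quota shared among midwives.
- The contamination argument in the Discussion makes sense only if whole work centres are allocated, and the following sentence there calls the unit a primary care unit.

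This stands as the more likely reading. It does not remove the contradiction, because the article defines PCN as nurses, Phase 1 recruits and commits individual professionals, and the conflicting sentences are the ones that fix allocation and the recruitment stop.

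It is also fair that the multilevel model and the undertaking to allow for the design effect in the main analyses partly meet the analysis concern, and that the exact random-effect specification may sit in an analysis plan that is not shown.

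Three stronger readings are tempting, and the document does not support them:
- **That 2.2 and 898 do not follow.** They follow exactly from the stated inputs, as does 36.
- **That 36 and 46 teams conflict.** The Setting section describes "46 PCTs from the province of Barcelona that provide health coverage to urban, semirural and rural populations", whereas 36 is the number needed. The product 46 × 25 = 1,150 differs from 898, but nothing says that all 46 teams recruit 25 each. More teams would not weaken the calculation, so the quota need not be lowered on this account.
- **That the trial is underpowered.** That requires an assumed two or more nurses per team, each recruiting 25, and a total still held at 898.

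**Conclusion.** The concern holds as a contradiction in operative text. The unit of randomisation and the quota of 25 are stated per team in the Abstract, Design and Sample size calculation, and per nurse, as PCN is defined, in Phases 2 and 4 and the Discussion. The sample size arithmetic is right. What is unsettled is whether it describes the clusters that are randomised and recruited.

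If PCN means team and 25 is the team total, nothing changes numerically. If teams are randomised and two nurses each recruit 25, the design effect is 3.45 instead of 2.2, and power is about 59-69% with 898 women in about 18 teams. That range rests on the assumed two nurses per team, an ICC of 0.05 at team level, 15% loss and a fixed total. If nurses are randomised, the protection against contamination claimed in the Discussion is lost wherever a team has nurses in both arms; the size of that effect cannot be derived from the document.

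**What to change.** Use one unit throughout. Since the context supports the team:
- Replace PCN by PCT in the randomisation sentence of Phase 2, the quota sentence of Phase 4 and the contamination paragraph of the Discussion.
- State the quota as 25 women per PCT, summed over its midwives.
- State how many PCTs were randomised.

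If allocation was in fact by nurse, say so, model midwife nested in PCT, report how many teams had both arms, and restate the design effect and the number of clusters for that unit.

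In the first case the cost is a few words and no extra women. In the second, the sample size justification has to be redone.

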### Data Collection

*Dependent Variables*: iodine deficiency (yes, no), is defined as ioduria less than 150 μg/lL

Independent Variables:

Variables related to the woman (information obtained through a individualized interview):

- Administrative: PCT, midwife, data collection date, patient code, telephone number.

- Sociodemographic: date of birth, level of education, etnia.

- Obstetric: n° of pregnancies brought to term; n° premature births, n° of miscarriges and n° of live births, trimester of gestation of the woman (1st, 2nd or 3rd).

- Related to smoking: smoker (no, yes), cigarettes/day prior to gestation, cigarettes/day during gestation, ex-smoker because of pregnancy, ex-smoker and time since cessation of smoking.

- Related to consumption of iodine-rich foods:

▪ Consumption of milk: glasses/day

▪ Consumption of yoghourt: units/week and type (whole or skimmed).

▪ Consumption of cheese: rations/week and type (cured, semi-cured and fresh).

▪ Consumption of vegetables: times/week, usual preparation (raw, fried, grilled/baked, steamed, boiled) and use of water in which they have been boiled (yes, no and no answer).

▪ Consumption of vegetables and garden produce: times/week.

▪ Consumption of fish: times/week, usual preparation (raw, fried, grilled/baked, steamed, boiled).

▪ Consumption of tinned tuna: times/week.

▪ Consumption of tinned sardines: times/week.

▪ Consumption of meat and derivatives: times/week.

▪ Consumption of eggs: units/week.

▪ Consumption of fruit: units/week and types (strawberries, pineapple, peaches, bananas, oranges and others).

▪ Consumption of nuts: times/week.

- Consumption of iodised salt: yes (time of consumption), no.

- Consumption of multiple vitamins containing iodine: yes (type), no.

- Consumption of potassium iodine supplement: yes (type), no.

- Related to the intervention: study group (intervention, non intervention), attendance to group workshop (yes, no).

Variables related to the midwife (information obtained through a individualised interview): years in the profession, primary care nursing training, mean number of visits per day.

Variables related to the PCT (information obtained through an individualised interview): population assigned, mean age of population assigned, whether or not it is a teaching center for residents, number of midwives.

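### With about 36 centres allocated by simple randomisation, adjustment for first-trimester ioduria should be fixed in advance; the plan as written allows it but does not secure it

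*Protocol article*

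**What the plan says.** Allocation is described in Description of the Study, Phase 2: "Using simple randomisation the centres distributed the IG and NIG at a proportion of 1:1". The article mentions no stratification, blocking, matching or minimisation. The Setting section describes the pool as "46 PCTs from the province of Barcelona that provide health coverage to urban, semirural and rural populations", and the sample size section concludes: "Therefore, 898 pregnant women and 36 PCT are needed".

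The Data Collection section defines the dependent variable as iodine deficiency (yes or no, cut-off 150 μg/L) without a time point. It then itemises the independent variables. Trimester is among them; first-trimester ioduria is not. The items at centre level are "population assigned, mean age of population assigned, whether or not it is a teaching center for residents, number of midwives", so type of setting is not listed, although the identity of the centre is.

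Phase 4 has ioduria requested in the first trimester in both arms and entered in the electronic file. The group workshop is Phase 5, in the intervention arm only. Phase 6 repeats ioduria in the second and third trimesters.

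The Statistical analysis section plans a baseline comparability analysis and a multilevel logistic regression on independent variables found significant in bivariate analysis. It also promises that all analyses will be adjusted for potential confounders and clinically relevant variables, none of which is named.

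**The concern.** With a few dozen clusters and unrestricted allocation, the arms can start from visibly different levels of deficiency. The best protection left after allocation is to condition on the outcome variable as measured before the intervention. The trial already collects it.

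The stated selection rule does not guarantee that it is used. A variable enters the model if it passes a bivariate test, or if someone later judges it a confounder or clinically relevant. That leaves the decision until after the data are seen. In addition, deficiency has no time point in its definition and trimester is listed as an independent variable. The first-trimester value could therefore be pooled with the later ones as an outcome, which would mix pre-workshop measurements into the treatment contrast.

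At stake are some power, and the credibility of the result if the baseline table shows an imbalance.

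**Working it through.** **Inputs from the sample size section.** Two-sided 5% level and 80% power ("an alpha error of 0.05 and a beta error of 0.20 in a bilateral contrast are considered"); a 15-point difference ("to detect a difference greater than or equal to 15% in the prevalence of iodine deficiency between the two"); control prevalence ("A proportion of iodine deficiency of 44% in the non intervention group is assumed"); 15% loss; intracluster correlation 0.05; 25 women per centre.

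**Reproducing the plan's figures.**
- For 44% against 29% with continuity correction, the two-proportion formula gives 173.6 per group, and 173.6 / 0.85 = 204.2. For 44% against 59% without correction it gives 173.1, and 173.1 / 0.85 = 203.6. Either matches 204.
- Design effect: 1 + (25 − 1) × 0.05 = 2.2.
- Total: 408 × 2.2 = 897.6, so 898 women; 898 / 25 = 35.9, so 36 centres.

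The plan's arithmetic holds.

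**Chance difference in baseline deficiency.** With 898 / 2 = 449 women per arm at baseline:
- SD = √(2 × 0.44 × 0.56 × 2.2 / 449) = √0.002415 = 0.0491, or 4.9 points.
- 95% range: ±1.96 × 4.91 = ±9.6 points.
- P(absolute difference above 5 points) = P(|Z| > 5 / 4.91) ≈ 31%.
- Sampling of individuals alone gives √(2 × 0.44 × 0.56 / 449) = 3.3 points. The clustering component is √(4.91² − 3.31²) ≈ 3.6 points.

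**What an imbalance does if left unadjusted.** The baseline-outcome correlation r is not in the article. Taking 0.3 to 0.7 as an assumption, and as a linear approximation with slope r at both woman and centre level, a 5-point imbalance shifts the later contrast by 5 × 0.3 = 1.5 to 5 × 0.7 = 3.5 points. For comparison, after 15% loss there are 21.25 women per centre, with design effect 1 + 20.25 × 0.05 = 2.0125. The effective size is 18 × 21.25 / 2.0125 = 190 per arm, and the standard error of the outcome difference is √((0.44 × 0.56 + 0.29 × 0.71) / 190) = 4.9 points. The shift is thus about 0.3 to 0.7 of a standard error.

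**Unequal numbers of centres.** If each of 36 centres is allocated independently with probability one half, an exact 18:18 split has probability 13.2%, and 22:14 or worse 24.3%. On the effective sizes above, power for 44% against 29% is about 86% at 18:18 and 84% at 22:14. The loss is about 2 points.

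**The case against.** **Adjustment is already promised.** The general commitment to confounders and clinically relevant variables could well cover first-trimester ioduria, and a baseline comparability analysis is planned. Naming covariates is often left to the analysis plan. This stands in part: a reader might infer that chance imbalance will remain in the effect estimate, and the article does not support that. But it does state a selection rule, bivariate significance, and it does itemise independent variables without this one. That is a stated choice for which a better one is available, not just detail left out.

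**Chance imbalance is not bias.** This stands. Over repeated randomisations the estimate is not systematically off because of it. The 4.9 points are ordinary sampling variation for a cluster trial of this size, calculated here with equal arms. They are already allowed for in the sample size, in the multilevel standard error and in the Discussion's commitment to account for the design effect. They do not measure harm caused by simple randomisation.

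**1:1 and simple randomisation.** A reader might infer that these contradict each other. They need not: 1:1 can be the allocation ratio, or half the centres may have been drawn. Unequal numbers would in any case cost little power.

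**Setting.** A reader might infer that the article shows deficiency differing between urban and rural centres. The Background reports differences between countries and affected zones in Spain, not between types of centre within Barcelona province. Setting can also be derived from centre identity. So the case for it is weaker than for baseline ioduria.

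**Precision.** A reader might expect adjustment to narrow the confidence interval by √(1 − r²). That formula is for linear models. In logistic regression, adding a prognostic covariate moves the conditional log odds ratio away from zero, and its standard error can fall or rise. The gain is mainly in power and in removing the imbalance that actually occurred.

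**Conclusion.** The point holds in a limited form. Allocation is unstratified over about 36 centres, so chance baseline differences of several points are likely (SD about 4.9 points, given 44%, design effect 2.2 and 449 per arm) against a 15-point target. This is imprecision that the planned standard error carries. The weakness is that the covariate rule and variable list leave adjustment for first-trimester ioduria possible but not secured, and leave open whether that value is treated as baseline or as outcome.

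The size of the benefit cannot be fixed from the article. It depends on the correlation between first-trimester and later values, which may be reduced because midwives act on detected deficiency between measurements. The shift of 1.5 to 3.5 points for a 5-point imbalance rests on the assumed range of 0.3 to 0.7 and on a linear approximation. Treating the value as pre-intervention rests on the order of Phases 4 and 5. This is a low-cost improvement to the analysis; it does not invalidate the design.

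**What to change.** In the Statistical analysis section, state that the multilevel logistic model comparing arms on second- and third-trimester deficiency includes first-trimester ioduria as a covariate regardless of bivariate significance. Fix its form (continuous, transformed or yes/no) before the analysis. State also that the first-trimester value is not pooled with the later values as an outcome in that comparison, and add it to the independent variables in Data Collection.

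Optionally, add type of setting (urban, semirural, rural), derived from centre identity, as a centre-level covariate.

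Allocation is reported in the past tense and needs no change. The cost is a few sentences and one to three more model terms: one for ioduria and up to two for setting. No new measurement is needed on the women.
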